## Abstract

**Background:**

Despite lack of outward signs, most individuals after non-disabling stroke (NDS) and transient ischemic attack (TIA) have significant cardiovascular and cerebrovascular disease and are at high risk of a major stroke, hospitalization for other vascular events, or death. Most have multiple modifiable risk factors (e.g., hypertension, physical inactivity, hyperlipidaemia, diabetes, tobacco consumption, psychological stress). In addition, accelerated rates of depression, cognitive decline, and poor quality of sleep have been reported following TIA, which correlate with poor functional outcomes and reduced quality of life. Thus, NSD and TIA are important warning signs that should not be overlooked. The challenge is not unlike that facing other 'silent' conditions - to identify a model of care that is effective in changing people's current behaviors in order to avert further morbidity.

**Methods/Design:**

A single blind, randomized controlled trial will be conducted at two sites to compare the effectiveness of a program of rehabilitative exercise and education versus usual care in modifying vascular risk factors in adults after NDS/TIA. 250 adults within 90 days of being diagnosed with NDS/TIA will be randomly allocated to a 12-week program of exercise and education (PREVENT) or to an outpatient clinic assessment and discussion of secondary prevention recommendations with return clinic visits as indicated (USUAL CARE). Primary outcome measures will include blood pressure, waist circumference, 12-hour fasting lipid profile, and 12-hour fasting glucose/hemoglobin A1c. Secondary measures will include exercise capacity, walking endurance, physical activity, cognitive function, depression, goal attainment and health-related quality of life. Outcome assessment will be conducted at baseline, post-intervention, and 6- and 12-month follow-ups. Direct health care costs incurred over one year by PREVENT versus USUAL CARE participants will also be compared. Ethical approval for the trial has been obtained from the relevant Human Research Ethics Boards.

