#### Sample Size

Systolic blood pressure, the most robust predictor of secondary vascular events [14], was selected as the outcome variable for sample size calculation. Using estimates obtained from our pilot study, a sample size of 119 in each group will have 80% power to detect a difference in means of 4.9 mmHg, assuming that the common standard deviation is 13.4 using a two group t-test with a 0.05 two-sided significance level. We have allowed for an overall attrition rate of 5% [55], thus increasing the sample size to 125 per group (250 in total). The trial will not be sufficiently powered to determine the effectiveness of the PREVENT intervention in reducing recurrent TIA, stroke or cardiac events. Thus, it will be exploratory in this regard and will help inform the design of a future, more extensive trial.

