### Outcome Measurement

Given the long duration and multi-modal nature of the interventions, a range of outcome measures will be used to ensure evaluation of relevant variables that span the domains of the International Classification of Functioning [66]. The variables and measurement tools that will be employed are summarized in Table 1. These measures were selected based on the primary and secondary aims of the trial, clinical relevance, psychometric qualities, and feasibility (availability, cost and administration time). Evaluations will be conducted over a 2-day assessment period at baseline, post-intervention, six months, and 12 months by trained assessors blinded to knowledge of study hypotheses and group assignment. At each assessment the assessors will be asked to record their 'guess' as to the group assignment of each participant.

**Table 1 T1:** Outcome variables, measurement tools and assessment schedule

Variable	Measurement tool	Baseline	Post-intervention	6-month follow-up	12-month follow-up
*Primary measures*					

Blood pressure	Sphygmomanometer [67]	√	√	√	√

Waist girth	Tape measure [68]	√	√	√	√

Lipid profile*	Biochemical analysis	√	√	√	√

Fasting serum glucose	Biochemical analysis	√	√	√	√

Haemoglobin A1c	Biochemical analysis	√	√	√	√

*Secondary measures*					

Aerobic fitness	Peak VO_2 _using maximal treadmill stress test (ramp protocol)	√	√		√

Lower extremity function	Short Physical Performance Test [69]	√	√	√	√

Walking endurance	Six-Minute Walk Test [70]	√	√	√	√

Physical activity	Step Watch™accelerometers	√	√		√

	International Physical Activity Questionnaire [71]	√	√	√	√

Fatigue levels	Fatigue Assessment Scale [72]	√	√	√	√

Cognition	Montreal Cognitive Assessment [73]	√			√

Mental health	Hospital Anxiety and Depression Scale [74]	√	√	√	√

Quality of sleep	Pittsburg Sleep Quality Index [75]	√	√	√	√

Tobacco use	Self-report, using a health passport	√	√	√	√

Health care utilization	Self-report, using a health passport	√	√	√	√

Medication adherence	Self-report, using a health passport	√	√	√	√

Health-related quality of life	Medical Outcomes Study Short-form 36-item Questionnaire [76]	√	√		√

Health-related goals	Goal Attainment Scaling [77]	√	√	√	√

Secondary vascular events**	Health record abstraction	√	√	√	√

*Includes total cholesterol, high-density lipoprotein cholesterol (HDL-C), low-density lipoprotein cholesterol (LDL-C), triglycerides

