### Data management and analysis

Data collected at each site will be recorded on standardized forms and entered into a secure database using a centralized, web-based data entry system that contains quality control checks (e.g., range checks, notification of missing data). An independent Data Safety and Monitoring Board, consisting a cardiologist, neurologist and a statistician, has been set up to review mid-point results (or at any time that a serious adverse event occurs) and inform the investigators on issues of trial safety.

Descriptive statistics will be calculated for dependent and independent variables. Demographic and clinical characteristics of subjects in the experimental and control groups will be compared on admission using 2-sample t-tests (continuous data) and Chi-square analysis (nominal data). Nonparametric methods will be used when assumptions of normality are violated. Similar analyses will be used to compare characteristics of (i) patients who consent to participate versus those who do not; (ii) subjects who complete the study versus those who withdraw, in order to determine the representativeness of the sample. A mixed effects analysis of variance with repeated measures will be used to model the treatment effects for variables that are interval or ratio and conform to the assumptions of normality (i.e., BP, waist girth, total cholesterol, HDL-C, LDL-C, triglycerides, serum glucose, hemoglobin A1c, peak VO_2_, Six-Minute Walk Test, step counts). Non-parametric tests (Mann Whitney and Kruskall Wallis tests) will be used for ordinal level data (i.e., International Physical Activity Questionnaire, Fatigue Assessment Scale, Montreal Cognitive Assessment, Hospital Anxiety and Depression Scale, Pittsburg Sleep Quality Index, Goal Attainment Scaling) or where a normal data distribution is not found. To control for baseline differences between groups, variables that are significantly different at baseline will serve as covariates in the analyses. Data will be analyzed on an intention-to-treat basis. Significant omnibus effects will be probed with t-tests, using the Bonferroni correction to control for multiple comparisons. Multiple regression will be conducted where appropriate to examine relationships among variables. Software will include Access and SAS version 9.1. Alpha level will be < 0.05.

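### Eight variables share primary status at a single 0.05 level, and the correction described does not extend across them, so the error over the primary set can be well above 5%

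*Protocol article*

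**What the plan says.** The Methods/Design part of the abstract reads: "Primary outcome measures will include blood pressure, waist circumference, 12-hour fasting lipid profile, and 12-hour fasting glucose/hemoglobin A1c". Table 1, under Outcome Measurement, puts the same measures under its primary heading and lists glucose and haemoglobin A1c on separate lines. Its footnote expands the lipid profile: "Includes total cholesterol, high-density lipoprotein cholesterol (HDL-C), low-density lipoprotein cholesterol (LDL-C), triglycerides".

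The Data management and analysis section says: "A mixed effects analysis of variance with repeated measures will be used to model the treatment effects". The primary variables it then names are "BP, waist girth, total cholesterol, HDL-C, LDL-C, triglycerides, serum glucose, hemoglobin A1c", that is, eight labels. On error control it contains two sentences: "Significant omnibus effects will be probed with t-tests, using the Bonferroni correction to control for multiple comparisons" and "Alpha level will be < 0.05".

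The Sample Size section gives SBP a special role in one respect: "Systolic blood pressure, the most robust predictor of secondary vascular events [14], was selected as the outcome variable for sample size calculation". The calculation there is a two-group t-test at two-sided 0.05. The primary aim, at the end of the Background, is worded as the reduction of vascular risk factors, in the plural.

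**The concern.** The sample size rests on one test of one variable at 0.05, whereas the outcome and analysis sections give primary status to eight variables at that same level. Nothing in the text ranks SBP above the others. The Bonferroni step begins only once an omnibus effect is already significant, so as written it governs the follow-up comparisons and leaves the eight omnibus tests themselves uncorrected.

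The broadly worded aim leaves room to read a favourable result on one variable, such as triglycerides or waist girth, as meeting it. On that reading, 0.05 is not the error rate of the primary conclusion, and a programme with no effect on any risk factor would have a substantial chance of being reported as successful on a primary outcome.

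**Working it through.** **Inputs from the protocol.** Sample Size: difference 4.9 mmHg, SD 13.4, two-sided 0.05, 80% power, 119 per group, raised to 125 for 5% attrition. Outcome Measurement and Data management and analysis: eight primary labels, one level of 0.05.

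**Assumptions.** One test per variable, no true effect on any variable, and a common correlation between test statistics, for which the document gives no figure.

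**Step 1. The plan's own figure.** By the normal formula, n = 2 × (1.960 + 0.842)² × (13.4 / 4.9)² = 2 × 7.85 × 7.48 = 117.4, so 118 per group. The exact t-test gives 118.4, so 119, with power of 80.2% at 119. Then 119 × 1.05 = 124.95, so 125. The sample size reproduces for a single SBP test at 0.05.

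**Step 2. How many tests.** BP (1) + waist (1) + lipids (4) + glucose (1) + HbA1c (1) = 8. If BP is assumed to be analysed as systolic and diastolic separately, the count is 9.

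**Step 3. Chance of at least one false positive.** For independent tests it is 1 − (1 − 0.05)^k:

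- k = 8: 1 − 0.95^8 = 1 − 0.663 = 33.7%
- k = 9: 1 − 0.95^9 = 1 − 0.630 = 37.0%

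For correlated tests, a simulation of k two-sided normal tests at 0.05 with equal pairwise correlation (500,000 draws) gives:

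| Assumed correlation | 8 tests | 9 tests |
|---|---|---|
| 0 | 33.7% | 37.0% |
| 0.3 | 29.9% | 32.7% |
| 0.5 | 25.0% | 26.9% |
| 0.7 | 19.1% | 20.2% |

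One assumed uneven structure (for example 0.9 between total and LDL cholesterol, 0.7 between glucose and HbA1c) gives 29% for eight tests and 32% for nine. Testing more than one model effect per variable would raise these figures.

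**Step 4. What correcting across the set would cost SBP.** Exact t-test, 119 per group:

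- Over eight: 0.05 / 8 = 0.00625, power 53%. Restoring 80% needs 194 per group, and 194 / 0.95 = 204.2, so 205 with attrition.
- Over nine: 0.05 / 9 = 0.00556, power 51%. Restoring 80% needs 198 per group, and 198 / 0.95 = 208.4, so 209 with attrition.

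Testing SBP first at the full 0.05 leaves its power at 80.2% with the planned 119.

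**The case against.** Five points can be made on the other side.

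- **The count.** A reader might take the primary list to contain systolic and diastolic pressure separately, and so quote nine tests and 27% to 37%. The documents do not support that as fact. Table 1 and the analysis section print blood pressure once, and diastolic pressure is not mentioned anywhere. Eight is the count as printed.
- **The success rule.** A reader might infer that the plan lets any one variable carry the trial. It does not say so, nor does it rule it out. If all eight had to succeed, the false-positive rate would be at most 5%, at a price in power. If SBP alone decided, the rate would be 5%. The figures in the table apply only where one success is enough.
- **The Bonferroni sentence.** It would be wrong to say that there is no multiplicity control. The sentence does not define its scope, and correction within a variable is only the likelier reading. What stands is that the text does not extend it to the omnibus tests across outcomes.
- **Matter for the analysis plan.** The missing decision rule is the kind of detail that a condensed article may leave out, and it is not held against the protocol here. The point rests on what is stated: several primaries, one level, and a correction tied to follow-up t-tests. A later analysis plan that ranked the outcomes would change this text as well as add to it.
- **The aim is plural.** For a multi-modal programme, making SBP the only outcome of interest would change the question. This stands, and it is why an ordered test is preferable to dropping the other variables from the primary aim.

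**Conclusion.** The concern holds in this form: eight variables are primary, each is modelled, one level of 0.05 is set, and the correction described does not span them. If one favourable result is taken as enough, the error over the primary set is about 34% with independent tests, 25% at correlation 0.5 and 19% at 0.7. With nine tests it is 37%, 27% and 20%. The correlations, the one-success reading and one test per variable are assumptions. Across the correlations tried, the one-success rate is roughly four to seven times the nominal 5%.

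The documents do not support concluding that the sample size is wrong. It reproduces, but for one SBP test, while the plan gives SBP no priority over the other primaries.

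**What to change.** Before anyone deciding on the change has seen results by group, state an order of testing:

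1. Test SBP first at two-sided 0.05, at one named between-group contrast and one named time point. There are three post-baseline assessments, so this has to be specified. It keeps the 119 per group and the 80% power.
2. Only if SBP succeeds, test the remaining risk factors with Holm at an overall 0.05. Otherwise report them as estimates with confidence intervals, labelled supportive.
3. State whether blood pressure also includes diastolic pressure, so that the number of tests in the second step is fixed.

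This keeps the plural risk-factor aim while holding the error over the set to 5%. Holm across all the primaries at once would also control it, but SBP power could then fall to as low as about 53% (51% over nine) at the planned size.

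Amend to match: the abstract's Methods/Design, the statement of aims at the end of the Background, Sample Size, Table 1, Data management and analysis, and the registry entry.

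No extra participants or measurements are needed. The cost is a substantive protocol amendment while the trial is enrolling, and a result on lipids, waist or glucose alone could no longer carry the primary claim.

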**Discussion:**

Whether timely delivery of an adapted cardiac rehabilitation model is effective in attaining and maintaining vascular risk reduction targets in adults after NDS/TIA is not yet known. We anticipate that the findings of this trial will make a meaningful contribution to the knowledge base regarding secondary stroke prevention.

**Trial registration:**

This trial is registered with the Clinical Trials.gov Registry (NCT00885456).

## Background

"Little stroke, big trouble", the theme of World Stroke Day 2008, speaks to the importance of heeding non-disabling stroke (NDS) and transient ischemic attack (TIA) as critical warning signs of further, more debilitating vascular events or death [1]. (Since the etiology and prognosis of NDS and TIA are essentially the same [2], hereafter they will be referred to as a single entity - NDS/TIA.) Until recently, the prognosis of NDS/TIA was deemed relatively benign because NDS/TIA appears to leave minimal impairment and no overt long-term effects [3]. However, many survivors of NDS/TIA have significant cardiovascular and cerebrovascular disease and a high probability of secondary stroke or death [4] - from 10% in the low-risk group, to 19% in moderate-risk group and 31% in high-risk group [5]. Thus, secondary prevention strategies are needed to avoid disabling stroke, the fourth leading cause of disease burden and the second leading cause of death among adults worldwide [6]. Moreover, recurrent strokes contribute disproportionately to the overall personal and economic burden associated with stroke [7] because of higher rates of institutionalisation and fatality than primary strokes [8].

Individuals presenting with NDS/TIA typically have significant atherosclerotic lesions throughout their vascular system and often manifest co-morbid cardiovascular disease (CVD) [9,10]. Not surprisingly, cardiac disease is the leading cause of death in stroke survivors [11,12]. It follows that CVD and stroke share common risk factors. Among the modifiable factors are hypertension, diabetes, dyslipidemia, physical inactivity, obesity, excessive alcohol consumption, and cigarette smoking [13]. Systolic blood pressure (SBP) is the most robust independent predictor of secondary vascular events such as myocardial infarction or recurrent stroke [14]. Diabetes is a strong independent predictor of stroke during the first year post-TIA, with rate of stroke recurrence being substantially higher in the diabetic stroke population [15]. Although dyslipidemia is less well established as a risk factor for stroke than for cardiac disease [16], recent guidelines for patients post-TIA include the administration of statin therapy with intensive lipid-lowering effects [17].

Both physical inactivity [18] and abdominal obesity [19,20] are independent risk factors for primary stroke. We documented that mean exercise capacity (peak oxygen consumption, VO_2_peak) at one-month post-stroke was only 60% of normative values, increasing to 71% at six months post-stroke [21]. Cigarette smoking has a causal relationship to atheroscelerosis, which explains why smoking is a major independent risk factor for stroke [22]. Heavy alcohol use (> 5 drinks/day) is a factor in stroke recurrence [23]. Metabolic syndrome, or clustering of vascular risk factors, is defined by the International Diabetes Federation as central obesity plus any two of the following: hypertension, hypertriglyceremia, low high-density lipoprotein-cholesterol (HDL-C), and insulin resistance [24]. This syndrome is critical in the development of recurrent ischemic stroke [25] and is also associated with silent brain infarction independent of other risk factors [26]. Control of the risk factors associated with metabolic syndrome is inadequate for people post-TIA or stroke [27] In a cohort of stroke survivors, 67% were overweight or obese, 80% had pre-hypertension or hypertension, 34% had low HDL and 45% had impaired fasting glucose [28]. Among patients post-stroke entering exercise studies, 99% of participants had at least one uncontrolled risk factor and 91% had two or more inadequately treated risk factors [28], figures comparable to what we reported in participants beginning stroke rehabilitation [29]. The problem is compounded by an acute lack of awareness and knowledge of cardiovascular risk factors among the NDS/TIA population [30]. Collectively, these findings suggest that there is considerable room for improvement in vascular risk factor management following NDS/TIA.

For people with CVD or diabetes, cardiac rehabilitation programs, consisting of exercise, education and lifestyle change counselling, improve all of the modifiable risk factors discussed above. Two large trials reported favourable effects of multi-modal cardiac rehabilitation on hypertension [31,32]. Cochrane reviews concluded that exercise alone [33], or the combination of exercise and dietary advice [34], also improve glycemic control (decrease in hemoglobin A1c) in people with type 2 diabetes. Benefits of group-based exercise sessions people with type 2 diabetes include reductions in SBP, hemoglobin A1c, fasting blood glucose levels, body weight and need for diabetes medication, as well as enhanced diabetes knowledge [35]. A ~50% reduction in risk of vascular events over 7.8 year period was reported following an intensive program of exercise, dietary modification and pharmacotherapy for people with type 2 diabetes [36]. Sustained moderate weight loss, achieved through lifestyle interventions (diet and exercise), is effective for the prevention and treatment of hypertension, diabetes and dyslipidemia [37,38]. Dietary advice alone has been shown to improve lipid profiles [34]. A systematic review found that comprehensive cardiac rehabilitation, but not exercise alone, induced reductions in total cholesterol, LDL-C and triglycerides, with no effect on HDL-C [33]. Reviews of multi-modal cardiac rehabilitation programs [33] and distribution of self-help education materials[39] have revealed little effect on smoking cessation.

Burgeoning evidence indicates that aerobic exercise not only reduces mortality in cardiac populations [32,40,41], but benefits mood [42], diminishes anxiety and depression [43], improves cognition [44,45] and decreases risk of dementia in vascular disease [46,47]. These additional benefits are relevant because people with TIA/NDS can have subtle but persistent neuropsychological deficits [48] similar to those accompanying hypertension [49]. As well, reducing depressive symptomatology - a condition found in up to 70% people post-TIA [50] - has been linked to decreased risk of recurrent cerebrovascular events [51].

There is good reason to suggest that risk factor management for NDS/TIA should be aligned with that of cardiovascular conditions, given that secondary risk factors, risk of recurrence, and the potential benefits of treatment are similar [2]. Preliminary support for a multi-faceted approach to secondary stroke prevention comes from a modeling study in which the authors concluded, ″At least four-fifths of recurrent vascular events in patients with cerebrovascular disease might be prevented by application of a comprehensive, multi-factorial approach″ [52]. A non-randomized study of a 3-month exercise program for patients within six months of NDS/TIA demonstrated improvements in walking endurance and exercise capacity [53]. Another non-randomized study of an 8-week educational program for people post-NDS/TIA demonstrated improved knowledge regarding stroke warning signs, medication adherence, blood pressure monitoring and reduction in salt intake [54]. A recent pilot randomized trial of a 10-week cardiac rehabilitation program for patients post-stroke demonstrated greater improvement in cardiac risk scores in the experimental group than the usual care group [55]. However, high-level evidence of risk factor reduction through non-pharmacological approaches is lacking [56]. For the most part, secondary stroke prevention trials have been short-term, focusing on pharmacological interventions (for example [57,58]) and endarterectomy for patient with surgical grade carotid stenosis [59].

Little provision is made in current health services for modification of lifestyle factors such as cardiovascular fitness, weight optimization and healthy eating for long-term secondary prevention in patients with NDS/TIA. This situation is at odds with recommendations supporting a combination of comprehensive lifestyle interventions and pharmacological therapy to prevent recurrent stroke and acute cardiac events in stroke survivors [60,61]. Indeed, Myint and colleagues [62] postulated that behavioral modifications may be as important as anti-hypertensive and cholesterol lowering agents in secondary prevention of stroke.

A major thrust in public health over the next decade will be to focus attention on identification and management of vascular risk factors. Although primary prevention is the ultimate goal, resources will need to be allocated to those who are at high risk and most likely to gain the greatest benefit. One such group is people who have experienced a NDS/TIA. The main objective of the PREVENT trial is to determine whether the timely delivery of a comprehensive program of secondary stroke prevention services and coordinated care can improve long-term vascular risk reduction for patients after NDS or TIA. The primary aim is to compare the effectiveness of a program of rehabilitative exercise and education (PREVENT) versus usual care (USUAL CARE) in reducing vascular risk factors in people who have had a NDS or TIA. Secondary aims are to compare between PREVENT and USUAL CARE groups (i) exercise capacity, walking endurance, daily physical activity, number of cigarettes smoked daily, medication adherence; (ii) fatigue, cognitive function, depression, health-related goal attainment and health-related quality of life; (iii) direct health costs incurred over a 1-year period; (iv) reduction in secondary vascular events, within the limitations in sample size and trial duration. We anticipate that, in comparison to USUAL CARE, timely delivery of PREVENT will produce clinically important and sustainable improvements in the outcome variables.

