### Participants

#### Inclusion Criteria

Participants will include males and females, over 17 years of age, who are within 90 days of diagnosis of first probable or definite TIA (symptom resolution in less than 24 hours) or ischemic or hemorrhagic NDS (National Institutes of Health Stroke Scale less than 6) [63] for which medical attention was sought.

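### Cigarettes per day is compared between whole arms under rules that would most directly ignore the baseline count; adjusting for it, with an added comparison in baseline smokers, is more sensitive at almost no cost

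*Protocol article*

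**What the plan says.** The aims at the end of the Background compare the two groups on a list of secondary variables that includes cigarettes: "Secondary aims are to compare between PREVENT and USUAL CARE groups (i) exercise capacity, walking endurance, daily physical activity, number of cigarettes smoked daily". The sentence is not limited to people who smoke. Nor is eligibility (Inclusion Criteria): "Participants will include males and females, over 17 years of age, who are within 90 days of diagnosis" of a first TIA or non-disabling stroke.

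Table 1 (Outcome Measurement) lists tobacco use as "Self-report, using a health passport", at baseline, post-intervention, 6 months and 12 months. A baseline count will therefore exist.

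Data management and analysis gives four relevant rules:
- Principle: "Data will be analyzed on an intention-to-treat basis".
- Interval and ratio variables that meet normality: "A mixed effects analysis of variance with repeated measures will be used to model the treatment effects for variables that are interval or ratio". The variables named there do not include tobacco use.
- Mann-Whitney and Kruskal-Wallis tests for listed ordinal scales, "or where a normal data distribution is not found". Tobacco use is not among the listed scales either.
- Covariates: "variables that are significantly different at baseline will serve as covariates in the analyses".

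No smoking prevalence, mean or SD of cigarettes per day, or target effect appears anywhere in the article.

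**The concern.** Participants who do not smoke at entry record zero cigarettes and cannot show a reduction. In a whole-arm comparison of follow-up counts they shrink the arm difference in proportion to the share of smokers, and the smoker/non-smoker split adds variance unrelated to treatment.

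The article's own rules point towards that comparison. A mostly-zero count is not normal, so it falls to the rank tests. A Mann-Whitney test takes no covariates, and no change score is mentioned. Even in a model that could take covariates, the baseline count would enter only if it happened to differ significantly between arms.

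The stake is a real effect in smokers being reported as no difference. Such a result would be readily believed, because the Background says that reviews of cardiac rehabilitation and of self-help materials "have revealed little effect on smoking cessation".

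**Working it through.** **Sample size used as input.** The Sample Size section plans 119 evaluable per group for systolic blood pressure (difference 4.9 mmHg, SD 13.4, two-sided 0.05, 80% power). The normal approximation gives 118 and the t-test 118.4, which rounds up to 119, with power 80.2% at 119. The stated figure reproduces. There is no corresponding figure for tobacco.

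**Assumptions (none is in the document).** Smoker share p of 10–40% in the closed form and 15–35% in the simulations. Baseline count in smokers of mean 15, SD 8. The effects are given with each result.

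**Closed form for a comparison of means.** Let the analysed value in smokers have mean m, SD s and arm difference d, and be zero in everyone else.
- Whole arms: difference p·d, variance p·(s² + (1−p)·m²), n per arm.
- Baseline smokers only: difference d, variance s², n·p per arm.
- The ratio of squared signal-to-noise gives the share of information kept: s² / (s² + (1−p)·m²) = 1 / (1 + (1−p)·k²), with k = m/s.

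With m = 12, s = 9, p = 20%: 81 / (81 + 0.8 × 144) = 81/196.2 = 0.41. At p = 15% it is 0.40 and at 30% it is 0.45. Mean 12 and SD 9 describe only the control arm (20% quit). Using both arms' values, 46–51% is kept.

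The result is driven by k. At p = 20% the loss is 17% for k = 0.5, 44% for k = 1.0, 64% for k = 1.5 and 76% for k = 2.0. It exceeds half only when k is above 1/√(1−p): 1.05 at p = 10%, 1.12 at 20%, 1.20 at 30%, 1.29 at 40%. If change from baseline is analysed, m and s refer to the change, k is smaller, and so is the loss.

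**Power of the Mann-Whitney test on follow-up counts.** Simulation with 119 per arm, quitting 20% v 40%, and a 20% cut in those who continue:

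| Smokers | Whole arms | Baseline smokers only |
|---|---|---|
| 15% | 13% | 31% |
| 20% | 16% | 42% |
| 25% | 20% | 50% |
| 30% | 24% | 57% |

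Repeat simulations of this scenario gave 12–22% v 35–61% and 13–26% v 33–59%. Over all runs the ranges are 12–26% and 31–61%. Type I error was about 4–5% in both analyses.

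**What using the baseline count changes.** Information lost by analysing whole arms rather than baseline smokers with the same method. Assumptions: 15–35% smokers, baseline-to-follow-up correlation 0.8, and three effects (4/day reduction; quitting 20% v 40%; that quitting plus 3/day reduction):

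| Analysis | Loss |
|---|---|
| t-test, follow-up only | 47–78% |
| Mann-Whitney, follow-up only | 41% to nearly 100% |
| ANCOVA on baseline | 5–17% |
| t-test on change | 16–32% |
| Mann-Whitney on change | 24–51% |

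In the quitting-plus-cut scenario at 15–30% smokers, a further run gave ANCOVA power of 49–77% both in whole arms and in baseline smokers, that is, essentially no loss. The range for ANCOVA is therefore about 0–17%.

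**The case against.** The strongest reply is that the article does not fix this analysis. The aims sentence names a variable. Tobacco use is in neither list of the analysis section, and a condensed article may leave the detail to a full protocol or analysis plan that is not shown. A whole-arm intention-to-treat contrast is also valid. This stands, and it makes the point an improvement rather than an error. The general rules are stated, however, and they lead most directly to an analysis without baseline.

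A reader might infer more than the document supports:

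- **That well over half of any tobacco effect is lost.** The document gives no inputs for such a figure, and it is not general. It depends on ignoring baseline and on k. With the baseline count in an ANCOVA the loss is at most about 17% on these assumptions.
- **That non-smokers are a fixed zero.** Baseline non-smokers can include ex-smokers, some perhaps recent, since entry is up to 90 days after diagnosis. They can relapse, and the whole-arm contrast captures that.
- **That a chance surplus of smokers in one arm would produce false positives.** At 20% smokers the arms' shares can differ by 1.96 × √(2 × 0.2 × 0.8 / 125) = 9.9 percentage points at the 95% limit. The test already allows for this variation, as the 4–5% type I error shows. The cost is precision.

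It is also fair to say that restricting to smokers does not make the outcome well powered: 31–42% at 15–20% smokers in the tabulated run, for an assumed effect that is not small.

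**Conclusion.** The point holds as a low-severity improvement. Read literally, the rules lead most directly to a whole-arm comparison of follow-up cigarette counts that leaves out baseline smoking. It is unbiased but insensitive: Mann-Whitney power of roughly 12–26%, against 31–61% in baseline smokers. These figures rest entirely on the assumed smoking prevalence, consumption and effect. The remediable cause is mainly the unused baseline count, and only secondarily the choice of whole arms. The Sample Size section powers systolic blood pressure only, and the Discussion calls the tobacco comparison exploratory, so no main conclusion of the trial depends on this.

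**What to change.** In the analysis section or the analysis plan:

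1. Analyse cigarettes per day adjusted for the baseline count, regardless of whether that count differs significantly between arms.
2. Add a comparison between arms among participants who smoked at baseline, including not smoking at 12 months (yes/no). Under Randomization Procedures allocation is revealed only after the baseline assessment, so this subgroup is defined before assignment is known and the randomised comparison is kept.
3. Report relapse or new smoking among baseline non-smokers as counts by arm.

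The cost is a few sentences; Table 1 already collects the data. The downside is that the smoker comparison rests on few people (at an assumed 20% smokers, 0.20 × 250 = 50) and leaves relapse prevention out of that contrast. This is why the adjusted whole-arm analysis and the relapse counts should stay alongside it.
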